## Methods

### Study design

This is a prospective, double-blind, single-center, randomized, controlled clinical trial designed to demonstrate the effects of PL extract on immune function. Recruitment starts in October 2020 and the trial ends in March 2021. Subjects are recruited via placards on outdoor billboards and banners in Daejeon University Cheonan Korean Medicine Hospital. All subjects receive written explanations and informed consent forms for the clinical trial protocol from a Korean medical doctor (KMD). The KMD also comprehensively explains the study to the recruited subjects, receives informed consent from them, and selects participants in the study based on detailed screening.

The study planned to recruit 98 subjects who will be randomly assigned in a 1:1 ratio to either the experimental group (PL 1000 mg) or the control group (placebo). The subjects take one 500 mg capsule twice daily for eight weeks, and this capsule contains either PL or dextrin, depending on the group they had been assigned to.

The variables we evaluated are NK cell activity, TNF-α, IFN-γ, IL-1β, IL-2, IL-6, IL-12, IgG1, IgG2, and IgM. Blood samples are taken for this laboratory test on the first day of participation, before the subjects has begun ingesting the test food, and 8 weeks later, at the end of the trial. The subjects visit the clinic three times and the clinical trial span a total of eight weeks (Table 1, Fig. 1).

**Table 1 Tab1:** Clinical trial process for the *Phellinus linteus* extract clinical trial protocol

Section	Screening	Visit 1 (baseline visit)	Visit 2 (during trial)	Visit 3 (trial end)
	(− 2 weeks to 0 days)	(0 days)	(4 weeks ± 5 days)	(8 weeks ± 5 days)
Prepare a written consent form	√			
Evaluate inclusion/exclusion criteria	√			
Examine subject information	√			
Assign screening number	√			
Assign random numbers to subjects		√		
Investigate medical history and medication history	√	√		
Conduct physical examination	√	√	√	√
Assess vital signs	√	√	√	√
Conduct clinical laboratory blood test	√	√		√
Conduct pregnancy test	√			
Observe upper respiratory tract infection symptoms		√	√	√
Distribute experimental/control foods		√	√	
Measure effectiveness-evaluation variables		√		√
Check adverse events			√	√
Identify concomitant drugs			√	√
Check compliance			√	√
Confirm cancelation and withdrawal criteria		√	√	√

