### Statistical analysis

Demographic data collected during screening will be tested using *t* tests (or Wilcoxon rank–sum tests) for continuous data. For categorical data, a chi-squared test (or Fisher’s exact test) will be performed. Effectiveness evaluation will be based on the results of the full analysis dataset. The per-protocol (PP) group will also be analyzed for reference. Statistical significance will be determined based on a significance level of 5%. If the difference between the two groups is normally distributed, an independent *t* test will be performed; if not, a Mann–Whitney *U* test will be performed. To test for differences before and after the treatment within a group, paired *t* tests will be used for normally distributed data; otherwise, Wilcoxon’s signed-rank tests will be used. The Shapiro–Wilk test will be performed to test the normality of continuous variables. When a difference between groups is observed, the drinking history variable will be considered for control variable, and additional covariate analysis will be performed. In the full dataset analysis, missing values will be replaced by the last observation carried forward. For the safety evaluation, the 95% confidence interval for each group will be determined by calculating the rate of occurrence of adverse reactions, and comparisons will be made between the groups. From the results of each laboratory test, continuous data such as vital signs will be compared with the baseline and analyzed using either a *t* test or a paired *t* test. If the assumption of normality is not satisfied, the Wilcoxon signed-rank test or the Wilcoxon rank–sum test will be performed. Categorical data will be analyzed using chi-squared tests and Fisher’s exact tests to determine whether there are differences between the groups in terms of the frequency and ratio of each category.

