### Withdrawal and dropout

Subjects who have taken the test food as part of the clinical trial for 8 weeks are considered to have completed the trial. Subjects are excluded from the trial in the following cases: violation of the inclusion/exclusion criteria (during screening only), request to withdraw made by the subject, occurrence of a serious adverse reaction or an adverse reaction that made continuation difficult, use of prohibited drugs that may have affected the efficacy-evaluation variables, loss of contact with the subject, consumption of medicines or functional health foods that may have affected the outcome, pregnancy during the trial period, and determination by the investigators.

All causes for dropping out of the study are documented in detail in the CRF. A laboratory test is also performed to assess the safety of subjects who dropped out. If an adverse event (AE) has occurred, follow-up observations are conducted and reported until the cause had been identified. In the case of serious adverse reactions, the IRB is notified immediately.

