### Safety

Side effects, such as AEs, adverse drug reactions, and serious adverse events (SAEs), are checked at visits 2 and 3. All AEs are classified and evaluated as mild, moderate, or severe. If an SAE occurred, it is reported to the IRB within 24 h of identification. The IRB reviews reports and develops appropriate follow-up measures. The organization that implemented the clinical trial makes every effort to protect the subjects’ safety. The principal investigator stops the trial for any subject who experienced an SAE and takes appropriate measures, such as withdrawing the subject, and, if necessary, removing the blinding. A safety evaluation is conducted based on the rate of occurrence of side effects. Subjects are compensated for damages caused directly by the test food, in accordance with the policy. The institution running the trial has insurance to cover any harm caused by the trial. Subjects damaged directly as a result of participation in the clinical trial are provided with appropriate measures and compensation.

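### The safety endpoint is named inconsistently: the statistical section compares adverse reactions, while the safety section evaluates side effects, a label that there covers all adverse events

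*Protocol article*

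**What the plan says.** The safety statistics are specified in one place, the Statistical analysis section of the protocol article. Each group's 95% confidence interval is to come from "calculating the rate of occurrence of adverse reactions", after which the two arms are compared. That section gives no rate, interval or comparison for all AEs or for SAEs. Its later sentence on categorical data follows from laboratory tests and vital signs and does not mention AEs.

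The Safety section describes a wider collection: "Side effects, such as AEs, adverse drug reactions, and serious adverse events (SAEs), are checked at visits 2 and 3". It adds "All AEs are classified and evaluated as mild, moderate, or severe" and then fixes the basis of evaluation: "A safety evaluation is conducted based on the rate of occurrence of side effects".

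Two other places bear on the point. Table 1, under Study design, has a row "Check adverse events" ticked at visits 2 and 3. The Withdrawal and dropout section says: "If an adverse event (AE) has occurred, follow-up observations are conducted and reported until the cause had been identified".

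**The concern.** In common trial usage an adverse reaction is an adverse event thought to be caused by the product, so it is a subset of adverse events. An analyst who follows the Statistical analysis section to the letter would first decide which events are reactions and then compare only those. An analyst who follows the Safety section would compare everything recorded. Both could say that they followed the plan.

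A placebo-controlled, double-blind trial can compare all events by randomised group and let the contrast show whether the product causes them. A comparison limited to attributed events puts a case-by-case judgement in front of that contrast, and the article gives no rule for the judgement. The open wording also allows the definition to be settled after the events are known. This matters because the Introduction sets out to confirm stability (apparently meaning safety) as well as efficacy, for an ingredient of a functional health food.

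**Working it through.** No arithmetic on safety can be reproduced, because the article states no AE rate, reaction rate or attributed share. The sample size is built on NK cell activity and does not bear on this point. The check is a comparison of the text.

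**Step 1. Which term is used where (protocol article)**

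| Section | Term | Used for |
|---|---|---|
| Study design, Table 1 | adverse events | scheduled check, visits 2 and 3 |
| Statistical analysis | adverse reactions | rate, 95% CI, group comparison |
| Withdrawal and dropout | adverse reaction, serious adverse reaction | reasons for exclusion from the trial |
| Withdrawal and dropout | adverse event | follow-up |
| Withdrawal and dropout | serious adverse reaction | notification of the IRB |
| Safety | side effects (AEs, adverse drug reactions, SAEs) | collection, basis of evaluation |
| Safety | AE | severity grading |
| Safety | SAE | reporting to the IRB, stopping for the subject |

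**Step 2. What each basis would count.** In usual definitions, adverse drug reactions and SAEs are both kinds of AE. The Safety section's list therefore amounts to all AEs. The Statistical analysis section's basis is either the attributed subset (literal reading) or all AEs (if the term is loose wording).

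**Step 3. Can the text decide between the readings?**
- For distinct terms: the Safety section lists AEs and adverse drug reactions as separate items in one sentence, and follow-up of an AE looks for its cause.
- For loose wording: IRB notification is tied to serious adverse reactions in one section and to SAEs in the other, and so is withdrawal of the subject. The Dosage calculation section also speaks of *related* adverse reactions in the preliminary study, a qualifier that would be redundant if the term already implied causation.
- No section defines adverse reaction, and the only event classification described is severity.

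The text does not decide.

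**Step 4. What a restriction would do, if it applied.** Let p be the proportion of a group with at least one AE, and s the share of those participants with at least one event called a reaction, with s between 0 and 1. The reported rate is then p × s, which cannot exceed p. The group difference changes from p(PL) − p(placebo) to p(PL) × s(PL) − p(placebo) × s(placebo). If s is the same in both groups, the difference shrinks by the factor s. If attribution instead removes the same number of background cases from each group of equal size, the difference is unchanged and there is less background around it. So the direction is fixed for the rate and open for the comparison.

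**The case against.** The strongest reply is that this is loose wording in a condensed article. The terms are interchanged in parallel rules, the Safety section already states the broader basis, and the schedule speaks of adverse events. Laboratory values and vital signs are compared without regard to attribution, so safety does not rest on a single attributed rate. Definitions and causality categories commonly sit in the full protocol or the SAP. Any attribution would also be made blind, so knowledge of the treatment group should not drive it.

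Much of this stands. A reader might infer that the plan counts only adverse reactions and that events judged unrelated drop out of the comparison. The article does not support that as a fact: it would need a definition of adverse reaction and a relatedness rating by which events are removed, and neither is described. A reader might also want to attach a loss of power. That is not supported either, because it would rest on assumed event rates and on attribution removing the same proportion from both groups; other assumptions reverse the direction.

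The reply does not remove the conflict itself. The missing definitions are not the point. Two statements that are in the article name different bases for one result, and the one attached to the statistics is, on its face, the narrower.

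**Conclusion.** The point holds as an inconsistency in the stated safety endpoint. The per-group rate, its interval and the group comparison are tied to adverse reactions in one section, and the safety evaluation is tied to side effects, including AEs and SAEs, in another. Exclusion of unrelated events follows only from a literal reading of the Statistical analysis section and from the usual meaning of adverse reaction; it is possible, not established.

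No numerical size is attached, for want of event rates. All that can be said is that a restriction would leave each group's reported rate equal or lower. The matter concerns safety reporting and does not touch the primary analysis of NK cell activity. It is still worth correcting before the data are examined, since the two readings could give different safety results from the same records.

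**What to change.** In the Statistical analysis section, base the rate, its 95% confidence interval and the group comparison on participants with at least one adverse event after first intake, regardless of relatedness. Give this for any AE, by severity, and for SAEs. Report adverse reactions as a subset, stating how an event is classed as one. Use the same terms in the Safety section in place of side effects.

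The cost is a change of wording and an extra table row. AEs are already collected at visits 2 and 3 and graded, so no new data are needed. The reported rates may look slightly less favourable than a count of reactions alone.

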### Withdrawal and dropout

Subjects who have taken the test food as part of the clinical trial for 8 weeks are considered to have completed the trial. Subjects are excluded from the trial in the following cases: violation of the inclusion/exclusion criteria (during screening only), request to withdraw made by the subject, occurrence of a serious adverse reaction or an adverse reaction that made continuation difficult, use of prohibited drugs that may have affected the efficacy-evaluation variables, loss of contact with the subject, consumption of medicines or functional health foods that may have affected the outcome, pregnancy during the trial period, and determination by the investigators.

All causes for dropping out of the study are documented in detail in the CRF. A laboratory test is also performed to assess the safety of subjects who dropped out. If an adverse event (AE) has occurred, follow-up observations are conducted and reported until the cause had been identified. In the case of serious adverse reactions, the IRB is notified immediately.

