### Dosage calculation

A dose of 200 mg/kg administered to mice for 1 week did not exhibit any specific toxicity. This effective dose was converted to a human intake dose of 960 mg/d (16 mg/kg/day), based on an adult body weight of 60 kg and a conversion factor of 0.08, which takes the relationship of body weight to body surface area into account. In a preliminary clinical study in which PL extract was ingested at 1000 or 2000 mg/day, no related adverse reactions were observed, and it was confirmed that immune function improved at 1000 mg/day. Therefore, the PL extract intake is set to 1000 mg/day for this study, based on the results of these preliminary clinical and animal studies.

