### Outcome measures

The primary outcome is the amount of change in NK cell activity. NK cells play a key role in immune function against viruses and have recently been shown to play an important role in anticancer activity [8]. NK cell activity is measured to evaluate whether immune function increased as a result of the treatment. The secondary outcome is the amount of change in WBC in the peripheral blood and in the levels of TNF-α, IFN-γ, IL-1β, IL-2, IL-6, IL-12, IgG1, IgG2, and IgM. Proinflammatory cytokines such as TNF-α, IFN-γ, IL-1β, IL-2, IL-6, and IL-12 are factors that regulate the inflammatory responses of tissues [9]. Immunoglobulins such as IgG1, IgG2, and IgM are involved in virus neutralization and aggregation reactions. They also play a major role in immunity against influenza [10]. Changes in immune function can thus be confirmed by measuring changes in cytokines and immunoglobulins.

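### Adverse-event follow-up is set to end when the cause is found, not when the outcome of the event is known

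*Protocol article*

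**What the plan says.** The rule stands in the Protocol article under 'Withdrawal and dropout': "If an adverse event (AE) has occurred, follow-up observations are conducted and reported until the cause had been identified". The sentence before it gives subjects who drop out a laboratory test for safety. The sentence after it requires prompt IRB notification of serious adverse reactions. Among the reasons for withdrawal, the same section lists "occurrence of a serious adverse reaction or an adverse reaction that made continuation difficult".

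The 'Safety' section has adverse events checked at visits 2 and 3 and graded as mild, moderate or severe. For serious events it adds "If an SAE occurred, it is reported to the IRB within 24 h of identification", followed by "The IRB reviews reports and develops appropriate follow-up measures". It also gives general undertakings on subject protection and insurance, and states: "Subjects damaged directly as a result of participation in the clinical trial are provided with appropriate measures and compensation".

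Table 1 schedules adverse-event checks at visit 2 (4 weeks ± 5 days) and visit 3 (8 weeks ± 5 days), and shows no later contact. Under 'Statistical analysis', the safety evaluation rests on "calculating the rate of occurrence of adverse reactions, and comparisons will be made between the groups".

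**The concern.** The cause of an event and its outcome are different facts, and they become known at different times. A rash or a rise in liver enzymes may be attributed to the test food, or to something else, on the day it is found and then last for weeks. A rule that ends follow-up at attribution lets such an event go while it is unresolved. The rule also misfires the other way: an event that has fully resolved but is never explained has no stated end to its follow-up.

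Two things are at stake. One is the protection of the individual subject, since knowing why an event happened does not show that the subject has recovered. The other is the safety record, which may lack the duration and final outcome of events. The undertaking to compensate for harm makes this practical, because compensation depends on the extent of the harm as well as its cause.

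The article states an end point and chooses the wrong one. This differs from leaving adverse-event detail to the full protocol, which would be no fault in an article.

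**Working it through.** No formula applies, and the plan gives no figure to reproduce. The check sets the stated end point beside every other provision that might carry an event to its outcome.

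1. **The stated limit ('Withdrawal and dropout').** Follow-up runs until the cause is identified. Resolution, stabilisation and outcome are not mentioned. While the cause is unknown, follow-up stays open, so the gap arises only for events whose cause is identified before they end.

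2. **Scheduled checks (Table 1 and 'Safety').** There are 2 adverse-event checks, at visits 2 and 3.
   - Event found at visit 2, subject continues: 2 − 1 = 1 check remains.
   - Event found or still open at visit 3: 2 − 2 = 0 remain.
   - Subject has left the visit schedule: 0 remain.

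   These figures count the schedule. They do not estimate harm. They show that the follow-up rule is the only remaining cover in the second and third cases, apart from the test in step 3.

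3. **Laboratory test for dropouts ('Withdrawal and dropout').** This is a safety assessment outside the Table 1 schedule and a real protection. No repeat is stated, however, and one test cannot show that an event still open at that time later ended. An event that is not visible in blood results would not be covered.

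4. **The IRB route ('Safety').** The sentence "The IRB reviews reports and develops appropriate follow-up measures" directly follows the rule on reporting serious events. No equivalent route is stated for non-serious events, which can still be graded moderate or severe.

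5. **General undertakings ('Safety', 'Data collection and monitoring').** The promises of protection, insurance and compensation, and the monitoring by the contract research organisation, apply to all subjects. None of them says when observation of an event ends.

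6. **The sharpest case.** A subject may be withdrawn for a reaction that made continuing difficult. The 'Safety' section lists adverse events and adverse drug reactions as separate terms. If 'reaction' in the withdrawal criterion implies attribution to the test food (an assumption), the cause may already count as identified at withdrawal. The follow-up duty, taken literally, could then end at once for someone who left because of harm.

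7. **Effect on the analyses.** The safety comparison uses rates of occurrence, and an event counts once it has occurred, however long it lasts. The primary outcome is laboratory-based: "The primary outcome is the amount of change in NK cell activity". Neither changes with the follow-up rule.

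8. **Size.** The article gives no expected rate of adverse events or of withdrawals because of them. The 15% dropout allowance in 'Sample size calculation' covers all reasons for leaving, and it is a planning figure, so it does not bound the number affected. The only relevant evidence is under 'Dosage calculation': in the preliminary study at 1000 or 2000 mg/day, "no related adverse reactions were observed". The size of that study is not given. This points to few cases but gives no number.

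**The case against.** The strongest reply is that a condensed sentence is being read as a complete stopping rule. It may be meant as a duty to establish causality: keep observing and reporting until the cause is known. Its place supports this, since it stands among the arrangements for documenting dropouts and not under 'Safety', where a general follow-up rule would be expected. It may also be loose wording for follow-up until resolution; the article's tenses are mixed throughout. The full protocol, approved by the IRB, may set proper end points. On that view the concern rests largely on what an article need not contain.

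Part of this stands. Other readings are possible, and the laboratory test for dropouts, the general undertakings and the monitoring make it unlikely that an ill subject would simply be abandoned. The reply is also right that no trial result is shown to change and that the schedule count does not measure harm.

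It does not remove the point. Even as a duty to find the cause, the sentence leaves cause as the only stated limit on observation, and nothing in the article corrects it. If it is a slip, it still needs correcting, because site staff act on what is written.

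**Conclusion.** The concern holds and is minor. The article states an end point for adverse-event follow-up, and the end point is the wrong one. The practical gap is confined to non-serious events whose cause is identified before they end, mainly in subjects who have left the visit schedule or whose event is still open at visit 3. Serious events are partly covered through the IRB. A continuing subject with an event found at visit 2 has one further check.

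The consequence falls on individual subject safety and on the completeness of the adverse-event record. The efficacy result and the comparison of adverse-reaction rates are untouched. How many subjects would be affected cannot be derived from the article. The conclusion assumes that the sentence is applied as worded and that no document not shown here overrides it.

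**What to change.** In 'Withdrawal and dropout', replace the end point with wording such as: *each adverse event is followed until it has resolved, stabilised or returned to baseline, or until the subject is lost to follow-up, whatever its cause and whether or not the subject remains in the trial.* Record the causality assessment as a separate item, so that it no longer determines when observation stops, and record the final outcome of each event.

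The change is one sentence. The 'Ethics' section already provides for protocol changes with IRB permission. The running cost is a few additional contacts or repeat blood tests for subjects whose event is unresolved at withdrawal or at week 8. Sample size, visit schedule and planned analyses stay as they are.
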